### **4.3. Provisional research timetable**

*These dates are provided for purely indicative purposes and cannot be considered definitive.*

| Tasks                                                    | Beginning  | End        |
|----------------------------------------------------------|------------|------------|
| Requests for regulatory authorizations                   | 02/01/2020 | 15/10/2020 |
| 1) GPs                                            | 01/12/2020 | 04/30/2021 |
| 1.1) KABP-6C assessment before intervention              | 01/12/2020 | 12/31/2020 |
| 1.2) Training                                            | 01/01/2021 | 03/31/2021 |
| 1.3) KABP-6C evaluation after intervention               | 01/04/2021 | 04/30/2021 |
| 2) TEENS, PARENTS and MIDDLE SCHOOL PROFESSIONALS | 01/12/2020 | 05/30/2021 |
| 2.1) KABP-6C assessment before intervention              | 01/12/2020 | 12/31/2020 |
| 2.2) EMM                                                 | 01/01/2021 | 03/31/2021 |
| 2.3) HPV vaccination                                     | 02/01/2021 | 04/30/2021 |
| 2.4) KABP-6C evaluation after intervention               | 01/05/2021 | 05/31/2021 |
| Analysis and valuation of results                        | 01/06/2021 | 01/06/2022 |

Duration of implementation of the research intervention: 7 months (December 2020 - June 2021)

Total duration of the research: 2 years

The training of GPs (see 8. Interventions evaluated in the context of the research) is an online training (e-learning type), with an equivalent of 4 hours of lessons, that the participating GPs will be able to access in at any time between January and March 2021.

The education, motivation, mobilization (EMM) sessions for middle school students and their parents (see 8. Interventions evaluated as part of the research) will take place in the middle school, with the active participation of health students. This education will be spread over several half-days for Grades 8 & 9 middle school students and a 2-hour information session for parents and all middle school teenagers. The directly targeted middle school students were restricted to Grades 8 & 9 students (and not 11-14 year olds, i.e. all classes in the middle school) for the following 2 reasons: (i) for a question of feasibility practice of implementing the intervention; (ii) education on HPV infection requires discussing the mode of transmission through sexual contact, but sexuality is only discussed from Grade 8, and so Directorate for school education prefers that we do not communicate on this subject in younger pupils. This component of the intervention will take place between January and March 2021.

Vaccination on the middle school site (see 8. Interventions evaluated as part of the research) will take place over 0.5 to 2 days for each eligible middle school, depending on its size and the number of middle school students wishing to be vaccinated. It will take place 4 to 6 weeks after the EMM intervention, between February and April 2021. Each middle school student concerned will be mobilized for approximately 30 minutes (trip to the infirmary, checking the health record and information, injection of the vaccine, monitoring of the effects of the vaccine for about fifteen minutes).

For each target population (middle school students, parents, GPs), a KABP-6C questionnaire will be offered before and after the implementation of the different components of the intervention.

In total, for middle school students benefiting from the EMM component, the duration of participation in the intervention will be a few days, between January and March 2021. For middle school students benefiting from the EMM and Facilitation of access to vaccination component, the duration participation in the intervention will be a few days, between January and April 2021. For GPs, the duration of participation in the intervention will be a few hours, between January and March 2021. In addition to participation in the interventions, the time taken to complete the questionnaires (KABP-6C, satisfaction questionnaire) before and after intervention(s) must be taken into account for each of the three populations above, estimated at approximately 15 minutes each.

Middle school students, their parents and GPs participating in PrevHPV research will be able to participate simultaneously in other research. There is no exclusion period.

## 5. SELECTION OF THE POPULATION

### 5.1. Populations under study

- **The target populations of the intervention are:**

- (i) GPs practicing in the municipalities randomized to groups 1, 2, 5,
- (ii) Middle school students enrolled in middle schools located in municipalities randomized to groups 1, 2, 3 and 4,
- (iii) Parents of middle school students attending middle schools located in municipalities randomized groups 1, 2, 3 and 4.

| Groups                                                   | Target populations | Middle school students | Parents of middle school students | GPs |
|----------------------------------------------------------|--------------------|------------------------|-----------------------------------|-----|
| Group 1 - EMM + Facilitation of access + Training of GPs |                    | X                      | X                                 | X   |
| Group 2 - EMM + Training of GPs                          |                    | X                      | X                                 | X   |
| Group 3 - EMM + Facilitation of access                   |                    | X                      | X                                 | /   |
| Group 4 – EMM                                            |                    | X                      | X                                 | /   |
| Group 5 - Training of GPs                                |                    | /                      | /                                 | X   |
| Group 6 - No intervention                                |                    | /                      | /                                 | /   |

*Populations targeted by the PrevHPV trial*

The effect of the intervention will be evaluated on:

- (i) Adolescents (girls and boys) aged 11 to 14 residing in the 90 municipalities participating in PrevHPV research (primary and secondary objectives),
- (ii) Parents of middle school students attending a middle school located in the 90 municipalities participating in PrevHPV research (secondary objective 2),
- (iii) GPs practicing in the municipalities randomized to groups 1, 2, 5 and 6 (secondary objective 2).

- **Others affected by this research**

Furthermore, National Education professionals as well as stakeholders (for example health students) who will participate in the various actions will be questioned using satisfaction questionnaires.

### 5.2. Inclusion and non-inclusion criteria

Inclusion in PrevHPV research is carried out at 2 levels:

- (i) the inclusion of participating municipalities,
- (ii) the inclusion of people participating in the research.

- **Inclusion of participating municipalities:**

The inclusion criteria for municipalities are as follows:

- Municipalities of the academies Aix-Marseille, Clermont-Ferrand, Créteil, Grenoble, Lille, Limoges, Lyon, Nancy-Metz, Nantes, Reims, Strasbourg, Toulouse, Orléans-Tours, Versailles,
- Municipalities in which a total of 1 to 4 middle schools (public or private) are located,

- Municipalities drawn at random from the group of 409 municipalities to be requested to participate in the research,
- Municipalities where all middle schools agree to participate in research.

- **Inclusion of people participating in interventions:**

Inclusion criteria

- ✓ For the intervention component 'Training of GPs' are:

- GPs practicing in the municipalities randomized to groups 1, 2, 5,
- Agreeing to participate in training in motivational interviewing and the use of the decision-aid tool.

**Will not be included:** (i) GPs having exclusively a Particular Mode of Practice, (ii) whose practice within the municipality is planned to stop during the first half of 2021, (iii) GPs with no internet access.

- ✓ For the intervention component 'Education, Motivation, Mobilization', are:

- Adolescents (girls and boys), enrolled in Grades 8 & 9 classes in middle schools (public and private) located in the municipalities randomized to groups 1, 2, 3 and 4,
- Parents of adolescents (girls and boys), enrolled in Grades 6 to 9 classes in middle schools (public and private) located in the municipalities randomized to groups 1, 2, 3 and 4, who agree to participate in an information/education session,

- ✓ For the intervention component 'Facilitation of access to vaccination', are:

- Adolescents (girls and boys), enrolled in middle schools (public and private) located in municipalities randomized to groups 1 and 3, in Grades 6 to 9 classes,
- Aged 11 to 14 on the date of injection, with possible catch-up among 15-19 year olds for those who have repeated a grade, in accordance with the recommendations,
- Not vaccinated against HPV on the date of offer of vaccination in middle school (April - May 2021),
- Whose parents (or representatives of parental authority) agree to the initiation of HPV vaccination in middle school,
- Not presenting a contraindication to HPV vaccination (hypersensitivity to the active substances or to one of the excipients of the vaccine, severe acute febrile illness on the date of injection)
- Affiliated with a social security scheme or beneficiary of such a scheme.

### **5.3. Selection methods**

Recruitment is carried out in two stages: (i) the selection of eligible municipalities, (ii) the selection of participating middle schools, making it possible to recruit the 90 municipalities, (iii) the randomization of the components of the intervention, and (iv) the identification of GPs to participate in the training.

1 Current vaccination recommendations (9-13) target girls and boys aged 11 to 14, with a catch-up possible from 15 to 19 years old. However, the vast majority of middle school students are between 11 and 14 years old. The exact age of middle school students on the planned date of the vaccine injection will be verified with the middle school administration. It is not possible to vaccinate middle school students under 11 years old, as this age is not indicated in the authorization for the vaccine.

2 The absence of HPV vaccination on the date of offer of vaccination in middle school will be verified with the parental authority at the time of the request for vaccination authorization, and checked against the health record at the time of injection.

3 The absence of contraindication to vaccination will be verified by the doctor of the vaccination center carrying out the injection on site at the time of the procedure, by questioning the student and checking the vaccination record.

4 Affiliation to a social security scheme will be verified with the middle school administration between the date of authorization from parental authority and the planned date of vaccination.

754 • **Selection of eligible municipalities:**

755 Information from academies (rectorates and diocesan management)

756 Each selected academy (rectorates and diocesan directorates) is informed in advance of the research by  
757 a note from the director of the DGESCO, and a letter detailing the experiment from the PrevHPV SC.

758 At the same time, 2049 municipalities in the selected academies meeting the inclusion criteria defined  
759 above were identified using data extracted from the data.education.gouv.fr website. These municipalities  
760 are then stratified according to the department and the FDep (ecological indicator of deprivation,  
761 dichotomized into 2 classes: > national average, < average). A random draw stratified on these two  
762 criteria made it possible to identify 409 potentially participating municipalities ([appendix 3](#)).  
763

764 • **Selection of participating middle schools:**

765 For each of the 409 municipalities selected, the principals and directors of each middle school located in  
766 the municipality are contacted by telephone, after having been informed by mail of PrevHPV research.  
767 This telephone contact allows us to provide additional information on the research and to request the  
768 middle school's agreement (or not) to participate. Ultimately, the participating municipalities are those for  
769 which all the middle schools located there (public + private) agree to participate in the research. The total  
770 number of municipalities to recruit is 90. If this number is not reached after contacting the 409  
771 municipalities previously selected, a second stratified draw - using the same methods as the first - is  
772 carried out from the initial file of the 2049 (- 409) municipalities.  
773

774 The principals and directors of each middle school are informed that, depending on the results of the  
775 randomization of the intervention components, participating in the research may involve benefiting from:

776 (i) EMM + facilitation of access to vaccination,

777 (ii) EMM alone,

778 (iii) neither (control group),  
779

780 A commitment to respect the result of the randomization will be requested from the principals/directors of  
781 the participating middle schools, that is to say to facilitate the implementation of the EMM components  
782 and/or facilitation of access to vaccination if they are concerned.  
783

784 • **Randomization of intervention components:**

785 For each of the 90 participating municipalities, a random draw stratified on the department and the  
786 deprivation group (according to the FDep) makes it possible to randomly assign one of the 6 research  
787 groups to each municipality. At the end of this draw, the DGESCO, the rectorates and the diocesan  
788 management, as well as the principals and directors of the middle schools are informed by postal mail  
789 from the PrevHPV's SC of the components the middle school will benefit from.  
790

791 5 The list of municipalities cannot be established until the middle schools agreeing to participate are known. Due to the COVID-19 lockdown, organizational  
792 changes within middle schools following the end of lockdown, the upcoming summer holidays and potential changes of principals in middle schools at the next  
793 school year, it was not possible to establish the list that will participate in the project next year. As soon as it is established, this list will be communicated to the  
794 members of the CPP  
795

In the same way, the mayors of the 90 participating municipalities are informed of the research and the allocation group of their municipality by post and the Departmental Councils will also receive a letter on this subject. They may also be contacted by telephone to discuss contextual elements that could facilitate the implementation of the intervention in their territory.

- **Identification of GPs to participate in the training:**

For each of the 45 municipalities in groups 1, 2 and 5, the list of GPs practicing within each of them is established. These GPs are then contacted by telephone, after having been contacted by mail, to verify their eligibility and offer them the opportunity to participate in motivational interview training and the decision-aid tool.

## **6. DISTINCTION BETWEEN USUAL CARE AND RESEARCH**

This research does not modify the usual care of the targeted populations. Regarding interventions with adolescents, we offer tools that may or may not be used because the project is essentially based on what already exists. Indeed, human papillomavirus (HPV) can be addressed through different disciplines and through different themes such as those linked to vaccination or sexuality education provided during cycle 4 (Grades 7 to 9).

Through the intervention offering vaccination within middle schools, the project simply aims to facilitate adolescents' access to vaccination by putting them in direct contact with Mobile Vaccination Teams.

**The only procedures added as part of this research are self-administered questionnaires (KABP-6C + satisfaction questionnaires).**

## **7. IMPLEMENTATION OF THE STUDY**

### **7.1. Selection**

See '5.3 Selection methods'

### **7.2. Inclusion, information, and participation agreement**

The selection process, information - participation agreement, and inclusion is as follows (see paragraph 5.3 Selection methods):

- Identification of eligible academies,
- Information from the rectorates of eligible academies and diocesan directorates of eligible departments by mail (DGESCO director letter + PrevHPV's SC letter),
- Identification of 409 eligible municipalities in eligible academies,
- Information by mail then telephone from the principals and directors of the middle schools of the 409 municipalities + request for participation agreement (→ identification of the 90 participating municipalities),
- Randomization of the allocation group (group 1 to 6) of the components for each participating municipality,
- Information for principals and directors of each middle school in their assigned group,
- Information for the mayors of each of the 90 participating municipalities and the corresponding

departmental councils,

- Information for GPs in municipalities in groups 1, 2 and 5, verification of eligibility and agreement to participate in training.

For each middle school of the 60 municipalities randomized to groups 1, 2, 3 and 4 (benefiting from EMM alone or EMM + facilitation of access to vaccination), the principal/director is in charge of informing the staff (health, teaching, administrative) of his middle school of the component they will receive. It will be essential that a referent be appointed within each middle school (school nurse/doctor, biology teacher, administrator, etc.) to be the main contact for the PrevHPV SC and to act as a link between the research teams and the actors in the field of experimentation.

Students and parents (or legal guardians) of each middle school in the 60 municipalities are informed by a letter at the end of 2020 by the referent and the principal/director of the component(s) (EMM or EMM + facilitation of access to the vaccination) deployed in their middle school between January and May 2021.

For the middle schools of the 30 municipalities randomized to groups 1 and 3 (benefiting from the 'Facilitation of access to vaccination' component), an information letter and collection of consent to vaccination are sent by the referent and/or each principal/school director, in January/February 2021, to the parental authority of each student enrolled in the school to propose the initiation of HPV vaccination at their child's school.

For each GP in the 45 municipalities randomized to groups 1, 2 and 5, an information letter on training (on motivational interviewing and the decision-aid tool) is sent by the PrevHPV SC. They are then contacted by telephone to check their eligibility and ask them to participate in the training.

The information intended for adolescents, their parents and GPs concerns the intervention carried out but also its evaluation methods (repeated cross-sectional survey KABP-6C).

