### 4.2. Research Method

A complete factorial design with 3 factors (= each of the 3 components) results in the constitution of 8 distinct groups. In our case, these 8 groups would be as follows:

- Group 1 benefiting from the 3 components 'Education, Motivation and Mobilization (EMM)' + 'Training of GPs' + 'Facilitation of access to vaccination',
- Group 2 benefiting from 'EMM' + 'Training of GPs',
- Group 3 benefiting from 'EMM' + 'Facilitation of access to vaccination',
- Group 4 benefiting from 'Training of GPs' + 'Facilitation of access to vaccination',
- Group 5 benefiting from 'EMM' only,
- Group 6 benefiting from 'Training of GPs' only,
- Group 7 benefiting from 'Facilitation of access to vaccination' only,
- Group 8 benefiting from none of the 3 components under evaluation (= control group).

However, not all of the above combinations are necessarily relevant. Indeed, it does not seem appropriate to offer vaccination on the school premises (facilitated access) to young people and their parents without them having first benefited from education on HPV infection and its vaccination (EMM), allowing them to make informed decisions. This is the reason why the 'Facilitation of access to vaccination' component will not be implemented without the 'EMM' component, and groups 4 and 7 will therefore not be formed.

Consequently, our partial factorial design will include the following 6 groups:

- **Group 1** benefiting from the 3 components 'Education, Motivation and Mobilization (EMM)' + 'Training of GPs' + 'Facilitation of access to vaccination',
- **Group 2** benefiting from 'EMM' + 'Training of GPs',
- **Group 3** benefiting from 'EMM' + 'Facilitation of access to vaccination',
- **Group 4** benefiting from 'EMM' only,
- **Group 5** benefiting from 'Training of GPs' only,
- **Group 6** benefiting from none of the 3 components evaluated (= control group).

Each group is made up of 15 municipalities (see 11.2 Sample size calculation), making a total of 90 municipalities participating in the PrevHPV trial.

The 'Training of GPs' component of the 45 municipalities in groups 1, 2 and 5 is implemented from December 2020 to April 2021.

The 'EMM' component of the 60 municipalities in groups 1, 2, 3 and 4 is implemented from January to March 2021 and the 'Facilitation of access to vaccination' component of the 30 municipalities of groups 1 and 3 is implemented. work from February to April 2021.

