A KABP-6C survey, at the individual level, repeated cross-sectionally (pre and post interventions) will make it possible to answer secondary objective 1 of the PrevHPV trial and thus to assess knowledge, attitudes, beliefs and practices. The KABP-6C questionnaire will be administered to volunteers in the following populations:

- Students, girls and boys, enrolled in Grades Eight and Nine in one of the public or private middle schools in the 90 municipalities of groups 1 to 6 before the implementation of the components in middle schools (December 2020) and after (May 2021).
- Parents, fathers and mothers of girls and/or boys enrolled in Grades Six through Nine in one of the public or private middle schools in the 90 municipalities of groups 1 to 6 before the implementation of the middle school components (December 2020) and after (May 2021).
- GPs practicing regular consultations with adolescents in the 60 municipalities of groups 1, 2, 5 and 6 before the implementation of the component (December 2020) and after (April 2021).

Costs and implementation indicators are collected prospectively by the referent of each middle school with the help of the PrevHPV project manager of the geographical sector concerned, as the different components of the intervention are implemented.

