### ***7.3. Request for exemption from the collection of consent***

The PrevHPV study is an interventional research in the field of public health, that is to say it is aimed at target populations (all adolescents attending middle school in the 90 participating municipalities and their parents) and not individuals specifically designated. The population-based nature of this research is difficult to reconcile with the collection of individual consent as requested by article L. 1122-1-1 of the Public Health Code. As a result, the CPP will be asked to be able not to collect individual consent from populations to participate in research, in accordance with article L. 1122-1-4 of the Public Health Code.

However, a letter (accompanied by an information note adapted according to the assigned group) will be sent to the families of all adolescents attending participating establishments via the schools in order to present the research to them.

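### The protocol does not place the baseline (T0) KABP-6C survey of students and parents before the letter telling families their allocated components, so the change analyses for secondary objective 1 may be biased

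*Protocol*

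**What the plan says.** **Order of information.** Protocol section 7.2 lists randomisation of the municipalities before any group-specific information. Students and parents in the 60 municipalities of groups 1 to 4 "are informed by a letter at the end of 2020 by the referent" and the principal of the component(s) to be deployed in their school. The same section adds: "The information intended for adolescents, their parents and GPs concerns the intervention carried out but also its evaluation methods", naming the KABP-6C survey. Section 7.3 sends a letter to the families of all adolescents in participating schools, "accompanied by an information note adapted according to the assigned group". That letter has no date.

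**Baseline survey.** Section 4.2 schedules the student and parent surveys "before the implementation of the components in middle schools (December 2020) and after (May 2021"). The timetable in section 4.3 gives 1 to 31 December 2020 for "2.1) KABP-6C assessment before intervention" and describes its dates as indicative.

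**GPs.** Section 4.2 places the GP survey "before the implementation of the component (December 2020) and after (April 2021"). It also says that the GP component "is implemented from December 2020 to April 2021", while section 4.3 gives January to March 2021 for the training. Section 7.2 has a training letter followed by a call for GPs in groups 1, 2 and 5, without a date. Section 7.4 has GPs in groups 1, 2, 5 and 6 telephoned about the survey.

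**Use of T0.** Section 11.3.2 (i) counts people who answer no on both intention and vaccination at T0 and yes on one of them at T1. It presents medians of T0–T1 differences and fits a difference-in-difference model with the control group as reference.

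**The concern.** A baseline serves a change analysis only if it is measured before the allocation can influence it. Here the allocation is already drawn, and the letter that discloses it falls in the same weeks as the survey. A family told that its school will run HPV education, or offer vaccination on site, may answer intention and attitude items differently from a family told that nothing will happen. It may also be more or less willing to answer at all, since participation is voluntary.

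Two consequences follow for secondary objective 1. First, a difference between arms already present at T0 is subtracted from the estimated effect. Second, someone who moves to yes after the letter but before T0 can no longer count as a positive change. Arm-dependent participation would add selection that neither analysis removes.

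This is a matter of trial conduct. A statistical analysis plan cannot restore a baseline collected after disclosure.

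**Working it through.** No figure stated in the protocol is in dispute, so there is none to reproduce. The check compares dates and then works through what a shifted baseline does.

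**1. Dates side by side (all Protocol)**

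| Event | Date given | Section |
|---|---|---|
| Randomisation of the municipalities | before all group-specific information | 7.2 |
| Letter naming the component(s), families in groups 1–4 | end of 2020 | 7.2 |
| Letter with group-adapted note, families in all participating schools | none | 7.3 |
| T0, students and parents | December 2020 | 4.2, 4.3 |
| Education component starts | January 2021 | 4.2, 4.3 |
| Training letter, GPs in groups 1, 2, 5 | none | 7.2 |
| T0, GPs | December 2020 | 4.2, 4.3 |
| GP component or training starts | December 2020 / January 2021 | 4.2 / 4.3 |

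For students and parents the letter and the survey fall in overlapping windows, and no section states which comes first. For GPs the date of disclosure is simply not given.

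**2. A further route.** In groups 1 to 4 the principal tells staff which component the school will receive (7.2), and student questionnaires are completed in class under a teacher or health professional (7.4). The person supervising T0 may therefore know the arm.

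**3. Effect on the difference-in-difference.** Let Δ be the true effect at T1 of being allocated to the arm, including anything the letter contributes. Let s_I and s_C be the shifts in T0 answers caused by information received before T0 in an intervention arm and in the control arm.

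- Estimate = (T1 − T0 in intervention) − (T1 − T0 in control)
- Expected value = Δ − (s_I − s_C) = Δ − d, where d = s_I − s_C

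If both arms shift equally, d = 0 and there is no bias from this source. If d is positive the effect is understated; if negative, overstated.

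**4. Illustration only.** The documents give no effect of the letter on answers and no target effect for intention. Every input below is an assumption, in percentage points.

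| Assumed Δ | d = 0 | d = 1 | d = 2 | d = 5 |
|---|---|---|---|---|
| 10 | 10 | 9 | 8 | 5 |
| 5 | 5 | 4 | 3 | 0 |

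With Δ = 10 and d = −2 the expected estimate is 10 − (−2) = 12.

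**5. Reach.** Under sections 3.1 and 11.3.1 the baseline for the primary outcome comes from the national reimbursement database and from vaccination and family planning centre records. KABP-6C answers do not enter it, so the coverage analyses are untouched.

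**The case against.** Several points count against a stronger reading.

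- **The order is open, not wrong.** A reader might infer that families learn their arm before answering T0 and that the estimates are therefore biased. The end of 2020 could fall after a survey run early in December, and section 4.3 calls its dates indicative. The documents support only that the order is not fixed. This stands.
- **The survey invitation may be a separate communication.** Section 7.4 sends it through each school's usual channels and does not say that it varies by group. Section 7.2 says what the information covers, not that invitation and disclosure travel together. This stands, but it does not stop the letter arriving first.
- **Control families are written to as well.** Under section 7.3 all participating schools' families receive a letter, so a general rise in awareness cancels. Only the part specific to the group matters. This stands and is built into d above.
- **GPs.** A reader might infer from section 4.2 that GP training starts during the GP baseline. The span given there coincides with the overall GP block in section 4.3 (December 2020 to April 2021), which also contains both GP surveys. Sections 4.3 and 4.4-style timetable text aside, the durations of participation stated at the end of section 4.3 repeat January to March 2021. What remains for GPs is an undated training letter and two statements to reconcile.
- **Size.** A reader might turn the illustration into an attenuation of 20 to 50% (d = 2 to 5 with Δ = 10). Those inputs are assumed and leave out zero and negative shifts, so no such figure can be claimed.

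None of this supplies the missing rule that T0 closes before disclosure.

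**Conclusion.** The concern holds in a limited form. For students and parents the protocol does not ensure that T0 is complete before the group-specific letter arrives. The no-to-yes change, the T0–T1 differences and the difference-in-difference model may therefore be biased, by an amount and in a direction that the documents do not give. Bias requires either a shift in T0 answers that differs between arms or participation at T0 that depends on the arm. Neither is shown to occur; neither is prevented.

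For GPs the point is weaker: the disclosure date is unstated, and sections 4.2 and 4.3 differ on when the component starts.

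The issue is confined to the KABP-6C analyses of secondary objective 1. The primary outcome is not affected. It is still worth correcting, because section 11.3.2 names no T1-only comparison of the randomised groups to fall back on and the remedy is cheap.

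**What to change.** 1. State in sections 7.2 and 7.4 that T0 is run under one neutral survey invitation, identical in all six groups for students and parents and in all surveyed groups for GPs.
2. Require T0 to be closed in each school, and for GPs in each municipality, before any group-specific letter or training invitation is sent.
3. Tie the group-specific letter to events: after T0 closes and before that school's component starts. A fixed January date would not be safe, because section 4.3 lets the education component start on 1 January 2021.
4. Date the letter in section 7.3 and the GP training letter in the same way, and reconcile the start of the GP component between sections 4.2 and 4.3.
5. Add a T1-only comparison of the randomised groups as a sensitivity analysis. It avoids a contaminated T0 but does not remove arm-dependent response.

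**Cost.** Mailings have to be sequenced, and families receive arm-specific information slightly later. No extra participants are needed. Section 7.2 already plans a separate mailing to parents in groups 1 and 3 in January/February 2021, so staged mailing looks feasible. One limit remains: staff who supervise T0 may still know the allocation unless they too are told after it closes.
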